### Trial design {8}

This study is a multicenter, placebo-controlled, double-blinded, randomized phase II trial with 132 adult patients. In a parallel group design, patients will be randomly allocated in a 1:1 ratio to inhale either aviptadil (67 μg three times a day) or normal saline (1 ml three times a day) for 10 days, or until hospital discharge, in addition to standard care. The study is conducted as a superiority trial.

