### Outcomes {12}

The primary endpoint is time to clinical improvement up to day 28, defined as the time (in days) from randomization to the decrease of at least two levels on the WHO-suggested nine-level ordinal scale (see Table 1) [55] or alive discharge from hospital, whichever occurs first. This standardized primary endpoint allows comparison with other efficacy studies in the context of the treatment of COVID-19.

**Table 1 Tab1:** WHO-Ordinal scale for clinical improvement

Patient state	Descriptor	Score
***Uninfected***	No clinical or virological evidence of infection	0
***Ambulatory***	No limitation of activities	1
	Limitation of activities	2
***Hospitalized: mild disease***	Hospitalized, no oxygen therapy	3
	Oxygen by mask or nasal prongs	4
***Hospitalized: severe disease***	Non-invasive ventilation or high-flow oxygen	5
	Intubation and mechanical ventilation	6
	Ventilation + additional organ support – pressors, RRT, ECMO	7
***Dead***	Death	8

From: WHO R&D Blueprint, Novel Coronavirus COVID-19 Therapeutic Trial Synopsis [55]

*RRT* renal replacement therapy, *ECMO* extracorporeal membrane oxygenation

Key secondary endpoints are:▪ Need for mechanical ventilation, non-invasive ventilation, and intensive care during hospitalization▪ Occurrence of multi organ dysfunction syndrome during hospitalization▪ Number of days requiring oxygen supplementation▪ Change from baseline to discharge of the following biomarkers in patients’ blood samples◦ C-reactive protein (CRP)◦ Neutrophil-lymphocyte ratio◦ Interleukin-6◦ Procalcitonin▪ Change from baseline to follow-up in patient-reported dyspnea, cough, and fatigue on a visual analog scale▪ Patient-reported impact on health by 12-item Short Form Survey version 2 (SF-12v2) at follow-up

Other clinical endpoints include the length of hospital stay until discharge or death (in days) and mortality rate. CRP, interleukin-6, and procalcitonin are measured at baseline, at least every seven days, and at discharge. The safety endpoints adverse events (AEs), including those leading to discontinuation of treatment, serious adverse events (SAEs), and death are also reported.

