### Sample size {14}

Based on the effect of aviptadil in previous trials described in the introductory section, we assume that patients in the experimental group will show a 1.75-fold hazard to have a clinical improvement as compared to patients in the control group (hazard ratio (HR) = 1.75) [42, 50]. Furthermore, based on previously published results for current standard care, we assume an overall probability of 80% for reaching the primary endpoint (clinical improvement) within 28 days (*d* = 0.8) [56, 57]. Group allocation shall be divided equally ($$\frac{1}{2}n={n}_1={n}_2$$).

Testing for two-sided equality in a Cox proportional hazards model at a significance level of *α* = 0.05 and aimed power of 80% (*β* = 0.2), we are applying the sample-size formula in Chow as follows [58]:$$n=\frac{{\left({z}_{\alpha /2}+{z}_{\beta}\right)}^2}{b^2\ast 0.25\ast d}=\frac{{\left(1.96+0.84\right)}^2}{{\mathit{\log}}^2(1.75)\ast 0.25\ast 0.8}\approx 125.2$$where *b* =  *log* (*HR*) =  *log* (1.75).

Estimating a drop-out rate of 3% and considering block randomization, we aim to include 132 patients into the study.

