## Statistical methods

### Statistical methods for primary and secondary outcomes {20a}

R will be used for all statistical analyses [59]. Primary and secondary endpoints will be summarized by group using descriptive statistics (mean ± standard deviation for normally distributed data, median and interquartile range for other continuous data, absolute and relative frequencies for categorical data). A log-rank test will be used to compare Kaplan-Meier curves for the primary endpoint “time to clinical improvement,” with failure to reach clinical improvement or death before day 28 being right-censored at day 28. Sensitivity analyses will be performed with “death” and “clinical improvement” as competing risks. For potential confounders that are not fully balanced by randomization, adjusted analyses for the primary outcome may be performed using Cox regression models to estimate hazard ratios with corresponding two-sided 95% confidence intervals to compare with the respective unadjusted Cox model. The proportionality assumption for the Cox proportional hazards models will be tested by assessing Schoenfeld residuals.

Treatment effects on binary secondary endpoints will be analyzed by means of chi-squared test, or Fisher’s exact test, in case expected sub-group size is smaller than five. For discrete secondary endpoints, group differences will be assessed using a Poisson or negative binomial regression, depending on the underlying distribution. Treatment effects on patient-reported severity of symptoms will be analyzed with an ordinal logistic regression and an additional longitudinal analysis with cumulative link mixed models. Effects on longitudinal changes in infection-related biomarkers will be assessed using mixed effect linear regression and analysis of covariance. Patient-reported impact on health at day 28 will be compared between the two groups by means of Student’s *T*-test, or Mann-Whitney-*U* test, depending on normality of the data.

All statistical tests will be performed using two-sided tests at the significance level 0.05. Detailed methodology for statistical analyses of the data collected in this trial is documented in a separate statistical analysis plan (SAP). The SAP is finalized before database closure and can be obtained from the authors upon reasonable request. A summary of the SAP is provided in Additional file 1.

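### The switch to Fisher's exact test in sparse tables is valid but conservative; Boschloo's exact test would recover up to about 18 points of power on rare secondary endpoints at almost no cost

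*Protocol article*

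**What the plan says.** In the protocol article, section {20a}, treatment effects on binary secondary endpoints are "analyzed by means of chi-squared test, or Fisher’s exact test, in case expected sub-group size is smaller than five". The level is common to all tests: "All statistical tests will be performed using two-sided tests at the significance level 0.05". I read the sub-group size as the expected cell count, which is the usual meaning. The text does not say whether the chi-squared test carries a continuity correction.

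The binary key secondary endpoints in Outcomes {12} cover ventilation (invasive or not), intensive care, and "Occurrence of multi organ dysfunction syndrome during hospitalization". No event rate is given for any of them. Mortality is in a separate sentence: "Other clinical endpoints include the length of hospital stay until discharge or death (in days) and mortality rate".

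On size, Trial design {8} has "patients will be randomly allocated in a 1:1 ratio to inhale either aviptadil", and Sample size {14} has "Estimating a drop-out rate of 3% and considering block randomization, we aim to include 132 patients into the study".

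**The concern.** Fisher's test conditions on the total number of events. When that total is small, few tables are possible, and the attainable error can lie far below 5%. Eligibility {10} excludes patients already ventilated or treated in intensive care, on high-flow oxygen or cPAP, or on vasopressors. Fewer than 10 cases of organ failure or invasive ventilation among 132 patients is therefore plausible. These endpoints are close to the progression the drug is meant to prevent, and under the rule they would get the test with the least power. An unconditional exact test also holds the level and gives up less. A second, smaller point is that the observed event count decides which test is applied.

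**Working it through.** **Inputs.** From the protocol: N = 132, 1:1 allocation, so 66 per arm; two-sided 0.05; the switch rule in {20a}. Assumed: all event rates.

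**The plan's own figure first.** Sample size {14}: (1.96 + 0.84)² / (ln(1.75)² × 0.25 × 0.8) = 7.84 / (0.3132 × 0.2) = 125.2, as stated. Then 126 / 0.97 = 129.9, so 130, raised to a multiple of four = 132. The protocol states no error rate or power for binary endpoints, so there is no figure of that kind to reproduce.

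**When the switch happens.** With equal arms the expected event cell is E/2 for E events in total. E/2 < 5 means E < 10. The same holds for non-events.

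**Method.** All 67 × 67 tables were enumerated. Error and power are Σ Bin(x; 66, p₁) · Bin(y; 66, p₂) over the tables that a test rejects. The Boschloo cut-off is the largest Fisher p-value that keeps the maximum error at or below 5%. It is 0.0711, and the maximum error is then 4.99%.

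**Real two-sided error at a common true rate**

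| True rate | Rule, chi-squared uncorrected | Rule, chi-squared corrected | Boschloo |
|---|---|---|---|
| 2% | 0.12% | 0.11% | 0.6% |
| 3% | 0.47% | 0.43% | 1.5% |
| 5% | 1.91% | 1.24% | 2.9% |
| 7.5% | 4.03% | 1.92% | 3.4% |

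These are averages over event totals. At a fixed total, Fisher cannot reject with 5 or fewer events; its error is 2.8% at 6, 1.3% at 7, 0.6% at 8 and 3.3% at 9.

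**Power**

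| True rates | Rule, uncorrected | Boschloo | Difference (points) |
|---|---|---|---|
| 0% vs 8% | 43.5% | 61.6% | 18 |
| 1% vs 9% | 39.6% | 51.9% | 12 |
| 1/66 vs 5/66 | 21.1% | 30.5% | 9.4 |
| 1/66 vs 6/66 | 34.8% | 44.0% | 9.2 |
| 1/66 vs 7/66 | 49.4% | 56.9% | 7.5 |
| 1/66 vs 8/66 | 62.9% | 68.2% | 5.3 |
| 2% vs 10% | 38.7% | 44.4% | 5.7 |
| 2% vs 12% | 56.8% | 59.9% | 3.1 |

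With a continuity-corrected chi-squared test the rule's power is 32.9% for 2% vs 10% and 49.0% for 2% vs 12%. The differences are then 44.4 − 32.9 = 11.5 and 59.9 − 49.0 = 10.9 points.

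The first row can be checked by hand. With no events in one arm, Fisher needs at least 6 in the other and Boschloo at least 5. For a binomial with 66 patients and rate 8%, those probabilities are 43.5% and 61.6%.

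**Which sparse tables change verdict.** For 0 vs 5, Fisher p = 2 × (66·65·64·63·62)/(132·131·130·129·128) = 0.058, and Boschloo p = 0.045. For 1 vs 7, Fisher p = 0.062 and Boschloo p = 0.045. No other table with fewer than 10 events changes: 0 vs 6 (Fisher 0.028) and 1 vs 8 (Fisher 0.033) are already significant.

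**Drop-out.** With 3% lost, 132 × 0.97 ≈ 128, or 64 per arm. Fisher's error over 2% to 7.5% is then 0.10% to 1.85%, almost the same.

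**The case against.** The strongest reply is that nothing here is wrong. Chi-squared with Fisher for small expected counts is the conventional rule, Fisher's level is guaranteed, and choosing among valid tests is partly taste. That stands: false positives are not inflated and the primary log-rank analysis is untouched.

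Four stronger readings are tempting, and the documents do not support them.

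- *The loss is 12 to 18 points whenever an arm has no or one event.* The 12 belongs to a true rate of 1%, which is 0.66 expected events. At one expected event the rule loses about 5 to 9 points.
- *The real error is never above 2%.* That holds for the whole rule only up to a true rate of about 5%. With an uncorrected chi-squared test it reaches 4.0% at 7.5%, because more tables then have 10 or more events.
- *Clear imbalances will be missed in general.* Only two sparse results change verdict, and each p-value moves from about 0.06 to 0.045.
- *These endpoints, and death, will be sparse and fall under this rule.* The protocol gives no rates and selects patients at high risk of ARDS. Sample size {14} assumes that 20% do not improve by day 28, about 26 of 132, so non-invasive ventilation or intensive care may well exceed 10 events. The rule is written for binary secondary endpoints, while mortality is listed among other clinical endpoints, so applying it to death is an inference.

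It is also fair that the detailed methods are deferred to an SAP that is not shown. The silence on continuity correction is therefore no finding in itself, and both cases are shown above. The choice of Fisher, however, is stated in the article.

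**Conclusion.** The point holds as a cheap improvement, not as a correction of an error. For rare binary secondary endpoints at 66 per arm, the stated rule runs well below its nominal level and gives up between about 3 and 18 points of power against a test that is also exact. The loss is largest when one arm has a true rate of zero and shrinks quickly as that rate rises. The size rests on assumed event rates, on reading the switch as an expected cell count below five, and on whether the chi-squared test is corrected. If these endpoints turn out common, the sparse branch is never used and this loss does not arise.

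**What to change.** In {20a} and the SAP, replace Fisher's exact test with Boschloo's unconditional exact test, preferably for all binary secondary endpoints. The observed event count then no longer chooses the test, and the level is held at 5%.

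If the switch is kept, use Boschloo in the sparse branch and state that the chi-squared test is used without continuity correction. The combined rule then has a maximum error of about 5.2%, which should be accepted openly. That maximum comes from the chi-squared branch at commoner rates, so the present rule has it too if its chi-squared test is uncorrected.

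The cost is one phrase and one R function, with no extra patients or data. Recruitment was ongoing at publication, and the SAP is to be final before database closure, so the change can be made prospectively and blind. The downsides are a less familiar test name and, if Boschloo is used throughout, slightly less power than the uncorrected chi-squared test for commoner events. In the same enumeration, 10% vs 20% gives 32.8% against 35.9%.

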### Assignment of interventions: allocation

#### Sequence generation {16a}

The group-allocating randomization code is a computer-generated sequence, using block randomization with block size of four. Each block determines assignment of four patients to the two groups, while two patients are assigned to the intervention group and two patients are assigned to the control group in a random order. Randomization is stratified by study center in order to account for differences in standard of care. Block randomization also accounts for differences in standard of care according to time elapsed since the start of the pandemic.

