### Data collection and management

#### Plans for assessment and collection of outcomes {18a}

All required patient data at baseline, during hospitalization, at discharge and follow-up are recorded on paper-based case report forms (CRFs). Trained study personnel at each site transfer the data into a web-based electronic case report form. A copy of the CRF used in the trial is available on reasonable request. Laboratory analyses comprise only standard parameters and are performed in the accredited in-hospital laboratories at each site. Patient dyspnea is assessed at inclusion and follow-up by means of the Medical Research Council dyspnea scale (MRC), which has been studied in a variety of respiratory conditions, including COVID-19. Patient-reported outcome is assessed at follow-up by means of the instrument SF-12v2, which is a validated survey for investigating health-related quality of life in a variety of both acute and chronic conditions, including lung diseases.

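### The day-28 SF-12v2 comparison lets observed normality choose between a test of means and a test of ranks, and neither named test uses study center or inclusion dyspnea

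*Protocol article*

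**What the plan says.** All references are to the Protocol article.

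- **Endpoint.** Outcomes {12} lists among the key secondary endpoints: "Patient-reported impact on health by 12-item Short Form Survey version 2 (SF-12v2) at follow-up". It is a follow-up value, not a change from baseline.
- **Collection.** Plans for assessment and collection of outcomes {18a}: "Patient-reported outcome is assessed at follow-up by means of the instrument SF-12v2". No SF-12v2 is taken at inclusion. The same section does record a baseline respiratory measure: "Patient dyspnea is assessed at inclusion and follow-up by means of the Medical Research Council dyspnea scale".
- **Test.** Statistical methods for primary and secondary outcomes {20a}: "Patient-reported impact on health at day 28 will be compared between the two groups by means of" a t-test or a Mann-Whitney U test, "depending on normality of the data". For this endpoint the article names no normality criterion, effect estimate or covariate.
- **Stratification.** Sequence generation {16a}: "Randomization is stratified by study center in order to account for differences in standard of care".
- **Adjustment elsewhere.** In {20a}, adjustment for imbalance is optional and confined to one endpoint: "adjusted analyses for the primary outcome may be performed using Cox regression models". Analysis of covariance is named in the same section, but for biomarkers.

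**The concern.** The t-test concerns a difference in mean score. Mann-Whitney concerns whether a score from one arm tends to exceed a score from the other. Under the stated rule, nobody knows which of these will be reported until the day-28 scores have been inspected. With roughly 60 patients per arm, a comparison of means does not need normally distributed scores unless skew is extreme, so the preliminary check protects against little.

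Both named tests are also plain two-group comparisons. The protocol stratifies by center because it expects care to differ between hospitals, and it records dyspnea at inclusion. With no baseline SF-12v2, these are the obvious covariates. At stake are a clear reading of one key secondary endpoint and some of its precision. The primary endpoint is not affected.

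**Working it through.** **Number analysed.** The article gives no figure for SF-12v2, so the number per arm comes from Sample size {14}. The stated formula reproduces: (1.96 + 0.84)² / (log(1.75)² × 0.25 × 0.8) = 7.84 / 0.0626 = 125.2. Rounding up to 126 and dividing by 0.97 gives 130; rounding up to a multiple of the block size of 4 gives 132. Conversely, 132 × 0.97 ≈ 128, or 64 per arm. Drop-out is defined as withdrawal of consent, and patients who die give no score, so 64 is an upper figure. The simulations of the rule use 60.

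**The two-stage rule.** The article names no normality test, so I assume Shapiro-Wilk in each arm at 0.05, followed by the t-test or Mann-Whitney at two-sided 0.05. The score shapes are assumptions too: SD 10, either normal or a constant minus a gamma variable. There are 4000 runs per row, and the shift is 0.5 SD.

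| Scores | Effect | Mann-Whitney chosen | t-test rejects | Mann-Whitney rejects | Two-stage rule rejects | Tests disagree |
|---|---|---|---|---|---|---|
| Normal | none | 9.9% | 5.2% | 5.1% | 5.2% | 1.9% |
| Normal | shift | 9.2% | 78.1% | 76.4% | 77.8% | 5.3% |
| Mild skew (gamma 16) | none | 46.0% | 5.3% | 4.7% | 5.4% | 2.2% |
| Mild skew (gamma 16) | shift | 46.7% | 77.2% | 77.3% | 78.0% | 6.0% |
| Strong skew (gamma 3) | none | 99.2% | 4.6% | 4.8% | 4.8% | 3.1% |
| Strong skew (gamma 3) | shift | 99.2% | 77.4% | 85.8% | 85.7% | 10.3% |
| Equal means, one arm skewed | shapes differ | 97.9% | 4.6% | 8.6% | 8.6% | 7.1% |

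The quantity compared depends on the shape observed: ranks are chosen in about 10% of trials with truly normal scores and in almost all with strong skew. With identical distributions, the rule rejects in 4.8% to 5.4%. In the last row the means are equal but the distributions are not. The rule rejects more often than the t-test there because it has moved to a different hypothesis.

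**Inclusion dyspnea.** Let r be its correlation with the day-28 score (assumed). Residual variance is multiplied by 1 − r². With 64 per arm, the difference detectable with 80% power is (1.96 + 0.84) × √(2/64) × √(1 − r²), in SD units. The equivalent gain in patients is 1/(1 − r²) − 1.

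| r | Variance reduction | Equivalent extra patients | Detectable difference | Power at 0.4 SD |
|---|---|---|---|---|
| 0 | 0% | 0% | 0.495 | 61.9% |
| 0.2 | 4% | 4% | 0.485 | 63.7% |
| 0.3 | 9% | 10% | 0.472 | 66.0% |
| 0.4 | 16% | 19% | 0.454 | 69.5% |

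**Center.** Simulated with 120 patients, 5 equal centers, blocks of 4 and 3000 runs. The share of variance due to center is assumed.

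| Share due to center | Type I error, unadjusted | Type I error, adjusted | Power at 0.5 SD, unadjusted | Power at 0.5 SD, adjusted |
|---|---|---|---|---|
| 5% | 3.8% | 4.5% | 79.2% | 80.4% |
| 10% | 4.3% | 5.3% | 80.0% | 82.8% |
| 20% | 2.6% | 4.3% | 80.8% | 85.7% |

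Ignoring center makes the t-test somewhat conservative and costs about 1 to 5 percentage points of power.

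**Where the fix could lose.** With 60 per arm, a constant shift of 0.4 SD and marked skew (gamma shape 1.5), the t-test has about 58% to 60% power and the two-stage rule, which then nearly always selects Mann-Whitney, about 80%. A linear model adjusted at r = 0.3 or 0.4 has, by the normal approximation Φ(0.4 / (√(2/60) × √(1 − r²)) − 1.96), about 63% or 67%.

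**The case against.** **The SAP may settle it.** The article refers detailed methods to a separate SAP that is not shown here, and covariates for a secondary endpoint are often left there. This stands in part: the article does not forbid adjustment, and a reader should not infer that the SAP contains none. But the normality rule is not silence. The article states it and names two unadjusted tests. A SAP that added a normality criterion would carry the rule out, and one that fixed a single model would depart from the article.

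**A rank test can still give an interval.** Mann-Whitney can be reported with a Hodges-Lehmann shift and its confidence interval in score points, and the planned software, R, provides it. This stands. The complaint is that the estimate is not fixed in advance, not that a rank analysis must lack one.

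**The harm is small.** Disagreement between the two tests is not an error rate, since each trial reports only one of them. The frequency of choosing Mann-Whitney depends on the skew assumed. Data analysts are blinded to allocation, which limits selective choice. All of this stands, and it keeps the point minor.

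**Adjustment is not a free gain.** The gain rests on unknown correlations, and under marked skew with a pure shift the rank test does better. This stands. A location shift is the case that favors rank tests, so the result is not general, but the proposed model cannot be presented as better in every scenario.

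**Conclusion.** The point holds as a minor improvement. The article makes the effect measure for a key secondary endpoint depend on the observed outcome data, and the tests it names leave out the stratification factor and an available baseline proxy.

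Two stronger readings are tempting, and neither is supported. The first is that the rule inflates false positives. With identical distributions its type I error was 4.8% to 5.4%; the 8.6% arises only where the distributions truly differ in shape. The second is that the unadjusted comparison is biased. Randomization protects it, and leaving out center or dyspnea costs precision only.

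The size of that cost is uncertain: a variance reduction of 4% to 16% for an assumed dyspnea correlation of 0.2 to 0.4, and about 1 to 5 points of power if center explains an assumed 5% to 20% of variance. The article gives no SF-12v2 distribution, correlation or between-center variation from which to narrow these ranges.

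**What to change.** Delete the normality rule. Prespecify, for each SF-12v2 summary score, one linear model with treatment, study center and inclusion MRC dyspnea score. Report the adjusted mean difference with its 95% confidence interval from robust standard errors, whatever the shape of the scores. Keep Mann-Whitney with the Hodges-Lehmann shift estimate and interval as a named sensitivity analysis, which also shows the reader whether skew matters.

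The cost is one or two sentences in {20a} and the SAP, with no new data. The article says the SAP is finalized before database closure and that recruitment was still ongoing, so the change was feasible at that stage. The price to acknowledge is possibly lower power than the rank test if scores are markedly skewed and the effect is a pure shift.
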